***Participation***

The study coordinator will provide a reminder a week before the interview (by phone/SMS). Participants will be reimbursed for their involvement in the sub-study and for travel expenses incurred, and receipts will be kept by the study coordinator.

***After the arranged interview***

Attempts to track participants will be made by the study coordinator if they did not attend their interview visit (by phone/SMS).

### Data management and analysis

Confidentiality of all information will be assured to all participants unless they report something that suggests that they or someone else whom they identify might be at risk of serious harm. In this case, a member of the research team may need to speak to their clinical team so that they are able to provide appropriate support. All survey and interview data will be de-identified and treated as strictly confidential. Personally identifiable data will be stored anonymously in locked filing cabinets at each study site or digitally in an encrypted file. Data will be identified only by the participant’s study ID and will be password protected with only the project investigators having access.

#### Phase 1

The qualitative intervention development and intervention process evaluation will be informed by thematic analysis [86]. Individual and focus group interviews will be recorded and initial codes will be generated from the audio data. Themes will be developed and reviewed from the initial codes. These themes will then be defined and named. These findings will be used to inform the intervention sessions in phase 2.

#### Phase 2: main study

Exploration of data will be conducted via pooled analysis as well as analysing by country, although the former is necessarily preliminary given issues of statistical power. The evaluation will present descriptive data on recruitment and retention rates and acceptability. We anticipate a retention rate of 68% based on previous studies [44]. If the retention rate in the study in each country is 68%, the 95% confidence intervals of this rate for each country (*n* = 94) would be ± 9.5% (i.e. confidence interval width of 19%). We feel that this is an acceptable level of precision to inform the planning of a future RCT and will be sufficient to answer the study research questions. Criteria for moving to a full trial will be based on a range of criteria, including acceptability (from individual interviews and rating scales), demand (based on recruitment and retention rates), implementation, adaptation (across the two settings) and limited efficacy. Reasons for refusal to enrol in the study will be assessed and comparisons will be made between participants and both clinic and national data on the population to assess the likelihood of selection bias.

For secondary outcomes, descriptive analysis will be conducted on frequencies, percentages, central tendency and variability of data. Missing data will be imputed if appropriate. The distribution of missing data will be assessed with Little’s Missing Completely at Random Test [87] before using Expectation Maximisation to impute missing data if the proportion of missing data is small. For multi-item measures developed or adapted for this study, Principal Components Analysis (PCA) will first be carried out using both orthogonal (varimax) and oblique (oblimin) rotations. Scree plots will be examined to determine the number of factors to extract and analyses will be re-run specifying the number of factors. Items will be dropped from the scale if factor loadings are low or if they load on more than one factor. If any items are dropped, PCA will be re-run. Cronbach’s alpha will calculated for the final total scale and its subscales, and item-total correlations will be examined.

The effect of the intervention on secondary outcomes will be carried out separately for each country. Two tailed tests will be used. Exploration via multivariate analysis will also be carried out if there is sufficient data to support this approach. Sufficient data refers both to missing data (although we will impute data if this is minimal, e.g., <5%) and to the number of observations (e.g., if attrition results in a lack of statistical power to investigate multivariate relationships).

Independent *t* tests (where parametric assumptions were met) and chi-squared tests will be used to compare baseline characteristics of those retained in the study to those lost to follow up to examine whether there are any systematic differences between these groups. We will interpret our findings on secondary outcomes in light of this ‘lost to follow up’ analysis. We will aim to obtain follow-up data from all participants enrolled in the study regardless of the extent of involvement in intervention activities.

The extent to which participants in the intervention condition naturally use HIV disclosure ‘change talk’ (language indicating preparation for and commitment to disclosing their HIV status) in the final individual session will be calculated using the Motivational Interviewing Skills Code (MISC) 2.5 coding manual [88]. The relationship between the frequency of disclosure change talk and any HIV status sharing at the 6-month data point will be calculated using logistic regression analysis.

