### Sample

The sample size will be 94 per condition (intervention or standard of care; 188 participants in total: 47 in each condition in each country). This sample size has been chosen to allow for study attrition so that at least 64 participants per condition will be retained in the study.

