#### Sample size calculation

The sample size of 32 in each condition in each country has been chosen to both assess primary outcomes, and to be sufficient to enable differences of between 0.5 and 1 standard deviation to be observed between conditions with 80% statistical power across secondary outcomes (e.g., changes in rates of HIV status sharing). Half a standardised difference would require 64 per condition, and one standard deviation difference would require 16 per condition.

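### The 0.5 SD end of the power statement is reached only with the countries pooled, yet effects are tested by country and the pooled analysis is the one described as limited by power

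*Protocol article*

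**What the plan says.** Three parts of the protocol article bear on this point.

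- **Sample and Sample size calculation.** Recruitment is 47 per condition per country, 94 per condition overall, so that "at least 64 participants per condition will be retained in the study". The justification begins "The sample size of 32 in each condition in each country has been chosen" and says that this number is meant, for secondary outcomes, "to be sufficient to enable differences of between 0.5 and 1 standard deviation to be observed between conditions with 80% statistical power". Changes in rates of status sharing are given as an example. The section adds: "Half a standardised difference would require 64 per condition, and one standard deviation difference would require 16 per condition".
- **Data management and analysis, Phase 2: main study (first paragraph).** Exploration is planned both pooled and by country, "although the former is necessarily preliminary given issues of statistical power". In that sentence the pooled analysis is named first, so it is *the former*. Anticipated retention is 68%.
- **The same section, on secondary outcomes.** "The effect of the intervention on secondary outcomes will be carried out separately for each country". Tests are two-tailed. No significance level is stated.

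**The concern.** The sample size section sets one range of detectable differences beside one sample size and does not say which end of the range belongs to which analysis. The 64 per condition behind the 0.5 SD end is a two-country total, whereas the analysis section places the effect tests inside each country, where 32 per condition are expected. The remark on power then points the reader away from the larger comparison.

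This affects how results will be read. The second hypothesis at the end of the Background predicts a higher rate of sharing under the intervention, and limited efficacy is among the criteria for moving to a full trial. A reader who attaches 80% power at 0.5 SD to the country-level tests would take a null result in one country as fair evidence against an effect of that size. It would be close to a coin toss. The same reader would be told to discount the pooled estimate for a reason that applies to the country estimates instead.

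**Working it through.** **Inputs.** From the article: 80% power; differences of 0.5 and 1 SD; two-tailed tests; equal allocation; 47 recruited per condition per country; 68% retention. Assumed: alpha 0.05, because it reproduces the article's figures, and a comparison of two means with a common SD.

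**Retained numbers.** By country: 47 × 0.68 = 31.96, about 32 per condition. Pooled: 94 × 0.68 = 63.92, about 64 per condition.

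**Reproducing the plan's figures.** Normal approximation: n per condition = 2 × (1.960 + 0.842)² / d² = 15.70 / d².

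- d = 0.5: 15.70 / 0.25 = 62.8, so 63. The exact t test gives 63.8, so 64.
- d = 1: 15.70 / 1 = 15.7, so 16. The exact t test gives 16.7, so 17.

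The stated 64 and 16 are therefore reproduced to within one participant. One-sided tests would give 50 and 13, which do not match, so two-sided 0.05 is the natural reading.

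**Power at 0.5 SD for each analysis.** Normal approximation: power = Φ(d × √(n/2) − 1.960).

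- By country, n = 32: 0.5 × √16 = 2.000; Φ(0.040) = 51.6%. Noncentral t: 50.4%.
- Pooled, n = 64: 0.5 × √32 = 2.828; Φ(0.868) = 80.7%. Noncentral t: 80.1%.
- By country with no attrition, n = 47: 0.5 × √23.5 = 2.424; Φ(0.464) = 67.9%. Noncentral t: 66.9%.

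**Difference detectable with 80% power.** Normal approximation: d = 2.802 × √(2/n).

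| Analysis | n per condition | Normal | t test |
|---|---|---|---|
| By country | 32 | 0.70 SD | 0.71 SD |
| By country, no attrition | 47 | 0.58 SD | 0.58 SD |
| Pooled | 64 | 0.50 SD | 0.50 SD |

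So the 0.5 SD figure belongs to the pooled comparison. Even perfect retention would not bring a single country to it.

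**The case against.** The best defence is that the sample size section gives a bracket, not a claim of 80% power at 0.5 SD in each country. It says openly that 0.5 SD needs 64 and 1 SD needs 16. The number 32 lies between them, and the country-level value of 0.71 SD lies inside the stated range. This stands: a reader might infer that the article makes a false power claim for each country, and its text does not support that. What remains is that the country-level value is never stated and the lower bound is left unattached to the analysis that yields it.

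Further points on the other side:

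- **The pooled analysis is not dropped.** It is planned explicitly. A reader who took the plan to rely on country tests alone would be mistaken.
- ***Former* may be a slip for *latter*.** If so, the authors already regard the country results as preliminary. The sentence is still wrong as printed. Once corrected, it would describe as preliminary the very level at which the effect tests are placed, so the two statements would still need reconciling.
- **This is a feasibility trial.** Primary outcomes are recruitment, retention and acceptability, and the precision of the retention rate is worked out separately. Limited efficacy is one of several progression criteria and carries no significance rule. Nothing requires significance in both countries, so the chance of two simultaneous significant results is not a relevant measure.
- **Separate country estimates serve a stated aim.** The article wants to assess suitability in each setting, and adaptation across settings is a progression criterion. Ranking the pooled test above the country results is therefore partly a preference. However, the reason the article gives for caution about pooling is power, not differences between countries.
- **The pooled 80% is itself conditional.** It assumes similar effects in both countries and independent observations. Three of the four intervention sessions are delivered in groups of seven or eight, and clustering could lower that figure.

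**Conclusion.** The concern holds as a mismatch between the power statement and the stated analysis, together with a reversed remark about power. By country, with 32 per condition, power at 0.5 SD is about 50% and the 80%-power difference is about 0.71 SD. Pooled, with 64 per condition, power at 0.5 SD is about 80%. The country analyses are the less powerful ones.

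These figures assume two-sided alpha 0.05 and a t test on means. The pooled figure also needs similar effects across countries and no clustering. Sharing is recorded as a frequency of new disclosures and a proportion of the network, so the SD scale is the article's own simplification and the percentages are approximate for that outcome.

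This is a should-fix point. It does not show that the sample is too small for the feasibility objectives, nor that by-country analysis is illegitimate.

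**What to change.** 1. In Sample size calculation, state the difference detectable with 80% power at each level, about 0.71 SD within a country (32 per condition) and about 0.5 SD pooled (64 per condition), with the alpha and the assumptions.
2. In Phase 2: main study, change *former* to *latter*, or give a different reason, such as possible differences between countries, for treating the pooled result as preliminary.
3. Reconcile these sections with the sentence placing effect analyses within countries. Attach the 0.5 SD claim to a pooled comparison stratified by country, which fits the stratified randomisation. Report country estimates with confidence intervals and say that they are not adequately powered tests at 0.5 SD.

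Adjusting for the baseline value of the outcome is an optional gain. Its size depends on a correlation that the article does not give.

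The cost is wording only, with no change to recruitment, randomisation or data collection, and it is best settled before outcomes are examined by condition. The price is a less favourable country-level figure than a reader may now assume.

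### The only stated missing-data method is reserved for small amounts of missing data, but the plan expects 32% loss, so it will not reach the 6-month secondary outcomes

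*Protocol article*

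**What the plan says.** All of the relevant text is in the protocol article.

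- **Forecast loss** (Data management and analysis, Phase 2: main study): "We anticipate a retention rate of 68% based on previous studies". The Sample section randomises "188 participants in total: 47 in each condition in each country" so that at least 64 per condition remain. The Sample size calculation works with 32 per condition per country.
- **Imputation rule** (same analysis section): "Missing data will be imputed if appropriate". Little's test comes first, "before using Expectation Maximisation to impute missing data if the proportion of missing data is small". "Small" is not quantified there. A later paragraph, on whether there is enough data for multivariate exploration, adds "although we will impute data if this is minimal, e.g., <5" per cent.
- **Effect analysis**: secondary outcomes are tested separately in each country, two-sided. No baseline adjustment is stated, and no method is given for missingness that is more than small.
- **Safeguards**: t tests and chi-squared tests will "compare baseline characteristics of those retained in the study to those lost to follow up", and the results inform interpretation. Follow-up is sought from everyone enrolled, whatever their attendance. Under Primary outcome measure, retention rates are to be calculated by site and by condition.

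**The concern.** The article fixes two things that do not fit together: a method confined to small amounts of missing data, and a forecast that about a third of follow-up outcomes will be missing. If the rule is followed as written, no imputation takes place at 6 months and the arms are compared among those who stayed.

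That comparison carries some weight. The second hypothesis, in the Background, is a between-arm difference in sharing at 6 months, and limited efficacy is one of the listed considerations for moving to a full trial. Participants in the intervention arm are asked to attend four 90-minute sessions, three of them in groups, and those in standard care are not. The kind of person who leaves could therefore differ between arms even if the retention rates are equal.

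The safeguards do not correct for this. Retention rates by condition would show unequal loss, but not a different type of loss. The retained-versus-lost comparison is not specified by condition and only informs interpretation. A non-significant Little's test does not establish that data are missing completely at random.

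**Working it through.** **1. Reproduce the plan's own figures** (two-sided alpha 0.05 assumed, because the article does not state it; power 80%).
- Size for 0.5 SD: the t-based calculation gives 63.8, so 64 per condition, as stated.
- Retention: 94 × 0.68 = 63.9 per condition and 47 × 0.68 = 32.0 per condition per country, matching the stated 64 and 32.
- Precision of retention: 1.96 × √(0.68 × 0.32 / 94) = 0.094, against the stated ±9.5%.

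The forecast is therefore used consistently throughout the design.

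**2. Set the forecast against the rule.**

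| | Total | Expected lost (32%) | Most that can be lost with under 5% missing |
|---|---|---|---|
| Per arm per country | 47 | 15 | 2 (0.05 × 47 = 2.35) |
| Per country | 94 | 30 | 4 (0.05 × 94 = 4.7) |
| Whole trial | 188 | 60 | 9 (0.05 × 188 = 9.4) |

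The ratio is 0.32 / 0.05 = 6.4. If true loss is 32%, the binomial probability of 4 or fewer lost out of 94 is about 3 × 10⁻¹¹. Even if true loss were only 10%, it would be 3.6%. The 5% is only an example, but no sensible reading of "small" extends to 32%.

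**3. Size of the possible bias.** The assumptions, none of which comes from the article, are: no true effect; 32% missing in both arms; baseline-outcome correlation 0.5; drop-out that depends on baseline in one arm only, with log-odds of 0.5 to 1.0 per SD.
- Spurious difference = correlation × shift in mean baseline among the retained.
- At log-odds 0.5 the shift is 0.152 SD, and 0.5 × 0.152 = 0.076 SD.
- At log-odds 1.0 the shift is 0.269 SD, and 0.5 × 0.269 = 0.134 SD.

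Simulation gave 0.07 to 0.14 SD. The sign follows the direction of the drop-out. Adjusting for baseline brings the difference to about zero, because drop-out in this scenario depends only on baseline.

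**4. Put that on the scale of the analysis.** With 32 per arm in a country, the standard error is √(2/32) = 0.25 SD.
- 0.07 / 0.25 = 0.28 and 0.14 / 0.25 = 0.56 standard errors.
- By the normal approximation, a nominal 5% test then rejects about 6% to 9% of the time.

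The sample size section targets differences of 0.5 to 1 SD.

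**5. Would it help to apply EM more widely?** A simulation with 47 per arm filled in 15 values per arm from a within-arm regression on one baseline covariate and treated them as observed. With assumed R² of 0, 0.25 and 0.5, type I error was about 18%, 15% and 10%. This describes an analysis that the plan does not propose. It shows only that relaxing the threshold is not a repair.

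**The case against.** The case on the other side has real force.

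- **The 5% figure is an example.** It sits in a sentence about optional multivariate exploration. A reader might infer a hard 5% ceiling on every effect analysis, but the text does not say so. What stands is that the general condition, "small", cannot cover 32%.
- **The completer analysis is inferred.** The article nowhere says that only completers will be analysed, and a separate analysis plan may add a method. Missing detail alone would be no finding in a journal article. The point stands because the article does state a rule, and that rule excludes the amount of loss on which the design is built.
- **Attrition by arm is not ignored.** A reader might infer that the plan cannot detect differential drop-out. That is wrong, since retention rates are reported by condition. Nor does the article say that the retained-versus-lost comparison pools the arms; it leaves this open.
- **Inflated type I error from single imputation.** A reader might infer error rates of 10% or more. Those arise only if EM values are treated as observed at 32% missing, which the plan's own condition rules out. At 5% missing the simulated rate was 5.6%. That the imputation is single is itself an inference, from the absence of any mention of multiple imputation or variance correction.
- **Direction and mechanism.** A reader might infer that the completer comparison must favour the intervention. The documents do not support a direction. If people leave because their sharing went badly, drop-out depends on the outcome, and an analysis under MAR would not remove that bias.
- **Feasibility setting.** The primary outcomes are recruitment, retention and acceptability. Reminders, tracing and follow-up regardless of attendance are all planned. This limits the severity but does not remove the mismatch.

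**Conclusion.** The point holds at moderate severity. On the plan's own forecast, the one missing-data method it states will not apply to the 6-month secondary outcomes: about 15 of 47 per arm per country would be missing. The per-country comparison then in effect rests on about 32 per arm, with no baseline adjustment stated. That this is a retained-participant analysis is inferred from the absence of any method for larger missingness and from a sample size built on those retained.

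The bias illustrated is modest: about 0.07 to 0.14 SD in either direction, or roughly 0.3 to 0.6 of a standard error per country. It rests entirely on the assumed correlation and attrition pattern. The primary feasibility outcomes are unaffected; what is exposed is the second hypothesis and the limited-efficacy consideration.

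**What to change.** For 6-month secondary outcomes, replace the rule based on small missingness, EM and Little's test with a baseline-adjusted likelihood-based model or multiple imputation under MAR. Use all randomised participants, and include condition, randomisation strata, the baseline outcome and predictors of drop-out. The intervention arm's baseline is taken just before the first session, so anyone lost between allocation and that session will have no baseline values. State how they are handled; multiple imputation can include them.

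Add one simple delta-adjusted sensitivity analysis, because outcome-dependent drop-out is plausible here and an MAR analysis does not address it. Present retained-versus-lost characteristics separately by condition. Do not extend single EM imputation to 32% missing.

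The cost is revised wording and modest extra programming, with no new data. The change should be made before outcome data are seen by arm, so that the treatment of a third of the follow-up data is not chosen afterwards.

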#### Phase 2: sub-study

The analysis of the qualitative data will be undertaken using thematic analysis [86]. Findings will be compared with the quantitative results to add further depth of understanding to the evaluation of the proposed intervention.

### Advisory groups

Two advisory groups will be formed (one in the UK and one in Uganda) to consult with on the progress of the study. The groups will involve key stakeholders, including young people living with PAH, partners, friends and family members, health care workers, health academics, and representatives from support organisations and policy making organisations. We will aim to recruit individuals with a spread of knowledge and expertise. The advisory group meetings will take place on four occasions over the life of the study—at the start of phase 1, prior to phase 2 recruitment, during phase 2 recruitment, and at the end of the study. The terms of reference of the groups will include the following:
Providing advice on recruitment and retentionProviding advice on the development of strategic partnerships, engaging stakeholders, and disseminationProviding a forum for discussion of key study issuesPromoting the studyProviding advice on intervention content

